The advantage of the traditional lymphadenectomy is that it thoroughly cleans the regional lymph nodes (LNs). However, there are important blood vessels around the 4sb and 12a LNs, such as the splenic artery and portal vein. The risk of vascular damage is higher, the operation is difficult, and the operation time is long. Patients with advanced lower third gastric cancer have a low rate of 4sb and 12a LNM, and the prognosis is poor. Therefore, we designed a new cleaning range. We divided the 4sb LNs into two parts, namely those at the root of the LGA and the peripheral LNs of the first branch. 12a LNs were divided into two parts, namely the anterior and posterior peripheral LNs of the PHA. According to the patient's condition, we will take the 4sb LND area as the first branch LNs of the LGA, saving those at the root, and take the 12a LNs in the anterior area of the PHA, saving those in the posterior area, in some patients. The purpose is to simplify the operation, shorten the operation time, reduce the surgical complications, and speed up the recovery of the patient while obtaining the same radical cure effect. However, the efficacy and safety of this new technique is still unclear.

Since the scope of 4sb and 12a LND is not uniform nationally and internationally and there are few studies on the effectiveness and safety of different anatomical scopes, clinical study on the scope of 4sb and 12a LND is necessary. Therefore, we designed this experiment to compare the pathology, safety, efficacy, and prognosis of the new and traditional methods of 4sb and 12a lymphadenectomy to provide a new, alternative lymphadenectomy for patients with gastric cancer.

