### Secondary outcomes

The secondary outcome has four parts: pathology data, efficacy index, safety index, and follow-up data. The pathology data comprises the 4sb lymph node metastatic rate, the number of 4sb LNs dissected, the number of 12a LNs dissected, and tumor pathological staging. The efficacy evaluation index comprises operation time, intraoperative blood loss, and postoperative recovery status (time to get out of bed, time to pass gas, time to liquid food intake, time to semi-liquid food intake, and postoperative hospital stay). The safety evaluation index comprises complications and mortality ≤30 days after surgery. Intraoperative complications include injuries of the hepatic artery, common bile duct, portal vein, spleen and pancreas. Postoperative complications include biliary fistula, delayed hepatic artery and portal vein hemorrhage, pancreatic fistula, and other pancreatic injury-related complications. Follow-up data comprises 3-year or 5-year disease-free survival and OS.

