### Sample size

The sample size was calculated using PASS 11.0 software. The 12a lymph node metastatic rate was used as the main result in the sample size calculation. This study assumes that the 12a lymph node metastatic rate in the experimental group is not inferior to the control group. According to published literature (9), the 12a lymph node metastatic rate of the control group is estimated at 9.1%. Combined with clinical practice, the non-inferiority threshold is set to −7.4%. The size of the two groups of patients was determined with a 1:1 design, setting a significance level of *α* = 0.025 (unilateral), power at 80%, and loss to follow-up at 10%. We expect 524 patients to be registered, with 262 patients in each group.

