### Statistical analysis

The normally distributed data will be expressed as mean ± standard deviation, and independent sample t-test will be used for groups differences. The non-normally distributed data will be expressed by a median, and the Mann–Whitney U test will be used for groups differences. The count data will be described as frequency and percentage and Fisher's exact test will be used for groups differences. The survival curve will be analyzed with the use of Kaplan–Meier, and the log-rank test will be used to evaluate groups differences. The Cox proportional hazards model will be used to evaluate the hazard ratio. *P* < 0.05 is set as the significance level.

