Huang (17) pointed out that the posterior boundary of 12a LND was defined as the anterior edge of the portal vein, so only the LNs in front of the portal vein were cleaned during the operation. Huang (14) published a new 12a LND sequence, suggesting that the portal vein should be exposed first and the LNs before the portal vein should be cleaned. However, we considered that the 12a lymph node metastatic rate is lower for advanced lower third gastric cancer, and LNM around the portal vein is even more rare. Therefore, we suggested that only the LNs area in the front of the PHA should be cleaned, retaining the LNs area around the portal vein. The same is true for the 4sb LNs. We suggested cleaning the LNs around the first branch of the LGA and retaining the LNs around the root of the LGA. Through such a cleaning method, under the premise of ensuring the radical cure of the tumor, the risk of damage to blood vessels and organs, and complications during surgery, are reduced.

Although ESMO, NCCN and JGCA regularly update the guidelines for treating gastric cancer, they are all updated in terms of indications of the extent of LND, and there is no further detailed update of the definition of LND (4–6). In addition, although there have been some studies on 4sb and 12a LNs, the majority are related to LNM and risk factors or survival rates. Therefore, we are currently conducting a clinical trial to establish a safer 4sb and 12a LND range, to reduce the complication rate of D2 lymphadenectomy while obtaining the same radical cure effect.

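### The aim of equal cure has only a log-rank test of difference behind it on survival, with no margin or confidence-limit criterion

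*Protocol article*

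**What the plan says.** The Introduction gives the purpose as a simpler, shorter operation with fewer complications, and to "speed up the recovery of the patient while obtaining the same radical cure effect". The Discussion repeats the aim: "to reduce the complication rate of D2 lymphadenectomy while obtaining the same radical cure effect". The Introduction also lists prognosis among the things to be compared.

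Survival is a secondary outcome: "Follow-up data comprises 3-year or 5-year disease-free survival and OS". Its analysis is in Statistical analysis: Kaplan–Meier curves, then "the log-rank test will be used to evaluate groups differences", then "The Cox proportional hazards model will be used to evaluate the hazard ratio". The error level for the section is P < "0.05 is set as the significance level", with no statement of sidedness.

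The only non-inferiority margin in the article, −7.4%, is in Sample size. It belongs to the 12a lymph node metastatic rate, and the 524 patients follow from it. No margin, event count or confidence-limit criterion is attached to disease-free or overall survival.

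**The concern.** The aim is sameness of cure, and the stated survival test looks for a difference. Failure to find a difference is not evidence of sameness, and the fewer the events, the easier it is to fail.

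The primary outcome does not fill the gap. It counts patients with a positive 12a node among the nodes removed. The experimental operation leaves the posterior 12a nodes and the 4sb nodes at the arterial root in place, so this rate cannot show whether leaving them costs cure. Survival can. The article chose non-inferiority framing for the 12a rate and did not carry it over to survival.

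At stake is the long-term report planned for 2030. If its log-rank test is not significant, the plan gives no rule for telling equal cure apart from too few events to see a loss.

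**Working it through.** **1. The plan's own figure.** Non-inferiority on a proportion, 9.1% in both groups, margin 7.4 points, one-sided 0.025, power 80%:

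n = (1.960 + 0.842)² × 2 × 0.091 × 0.909 / 0.074² = 238 per group (rounded up).

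238 × 1.10 = 261.8, so 262 per group and 524 in total. The stated size is reproduced, and survival plays no part in it.

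**2. Inputs for survival.**
- Evaluable patients: 262 × 0.90 = 236 per group (stated size and stated 10% loss).
- Follow-up: five full years, the last visit in the schedule (completeness assumed).
- Control 5-year survival: 35.9%, the only survival rate in the article. It is national overall survival for gastric cancer, not for this population. A resectable M0 group should do better, so 50% and 70% are added as assumptions.
- Hazard ratios 1.25 and 1.30 as illustrations; the article names none.
- Exponential survival, proportional hazards, two-sided 0.05 (assumed).

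**3. Formulas.** Events D = 236 × [(1 − S) + (1 − S^HR)]. Power = Φ(ln(HR) × √D / 2 − 1.96). The miss probability is 1 − power.

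Example, S = 0.359 and HR 1.25: S^HR = 0.278, so D = 236 × (0.641 + 0.722) = 322. Power = Φ(0.2231 × 17.94 / 2 − 1.96) = Φ(0.041) = 0.516. Miss = 48%. Here 5-year survival has fallen from 35.9% to 27.8%.

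| Control 5-year survival | HR | Events | Miss |
|---|---|---|---|
| 35.9% (article) | 1.25 | 322 | 48% |
| 35.9% (article) | 1.30 | 325 | 34% |
| 50% (assumed) | 1.25 | 255 | 57% |
| 50% (assumed) | 1.30 | 258 | 44% |
| 70% (assumed) | 1.25 | 156 | 72% |
| 70% (assumed) | 1.30 | 158 | 62% |
| 70% (assumed) | 1.50 | 169 | 25% |

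Simulated log-rank tests for HR 1.25 and 1.30 (4,000 per setting) agree within about 2 points.

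**4. Sensitivity.** For HR 1.25 to 1.30 over the same survival range, the miss probability runs from 34% to 72%. With all 524 patients and no loss it runs from 30% to 69%. At 3 years, with 472 patients, it runs from 47% to 80%.

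**5. What an interval could exclude.** If the true hazard ratio is 1, 472 patients give about 303 events (35.9% survival) or 142 (70%).
- Expected upper 95% limit: exp(1.96 × 2 / √D) = 1.25 at 303 events and 1.39 at 142.
- Hazard ratio excluded with 80% power: exp(2.80 × 2 / √D) = 1.38 and 1.60.
- For comparison, 80% power to exclude 1.25 needs 4 × (1.960 + 0.842)² / ln(1.25)² = 631 events, more than the 524 patients. Excluding 1.30 needs 457.

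**The case against.** The strongest reply is that the article contains no faulty decision rule. Equal cure appears as a purpose in the Introduction and Discussion, and neither place ties it to disease-free or overall survival by name. A reader might infer that P > 0.05 is to be read as equal cure, but no section says so. That part of the reply stands. What remains is narrower: the listed outcomes that observe cure have a stated test that cannot support the stated aim, and nothing else in the plan can.

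Second, survival is secondary, and sizing a trial on its primary outcome is normal. This stands too: low power for survival is not in itself a fault.

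Third, a Cox hazard ratio is planned, and a condensed article may leave its interval and margin to a fuller document. This stands in part. Missing detail would be no finding. The choice of a difference test for a sameness aim, however, is stated in the article.

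Fourth, it is tempting to say that a real loss would usually go unseen. The table does not support that: four of its seven settings have a miss probability below one half, and at HR 1.50 it is 25%. The right word is often. The range also rests on assumed inputs, and disease-free survival should yield more events than overall survival, hence a somewhat lower miss rate at the same hazard ratio.

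Fifth, under Study design the surgeon allocates patients, and experimental patients found node-positive move to the control group. The Conclusion concedes possible selection bias. The transfer worsens control prognosis and can pull the hazard ratio towards sameness, so a margin applied to an unadjusted ratio could reassure falsely. This stands and shapes the fix.

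**Conclusion.** The point holds as a mismatch between test and aim. The article seeks equal cure and offers, on survival, a log-rank test of difference and a hazard ratio with no criterion. A non-significant result could not establish what the trial sets out to show.

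Under the assumptions listed above, the test would miss a 25% or 30% higher hazard in 48% or 34% of trials at the article's own 35.9% survival. The figures are 57% or 44% if control survival is 50%, and 72% or 62% if it is 70%. A real loss would therefore often, though not always, give P > 0.05. The exact range depends on assumed inputs; the conclusion does not, since it already holds at the article's own survival figure. The plan should be changed, but the point does not touch the primary outcome or the sample size.

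**What to change.** In Statistical analysis:
- Base any statement about equal cure on the two-sided 95% confidence interval of the Cox hazard ratio and of the 3- and 5-year differences in disease-free and overall survival (experimental minus control).
- Report the largest loss that the interval excludes. Claim sameness only if the interval clears a margin fixed before survival data are seen. The interim analysis at 262 patients covers secondary outcomes, so the margin should be fixed before it.
- State that P > 0.05 is not evidence of equal survival, and keep the log-rank test as descriptive.
- Take the hazard ratio from a model adjusted for prognostic factors already collected, such as age, body mass index, concomitant disease and clinical stage. Say that the result will be read in the light of surgeon allocation and the transfer of node-positive patients. Adjustment for preoperative factors cannot fully undo a transfer made on findings during the operation.

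The cost is a few sentences, with no extra patients and no change to the surgery. The price is a more modest conclusion. Even with a true hazard ratio of 1, the expected upper limit is about 1.25 to 1.39, and the hazard ratio that can be excluded with 80% power is about 1.38 to 1.60. With a margin of 1.25 or 1.30 the trial may well be unable to claim sameness, and would then report only what it has ruled out.

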### Interim analyses

When the number of enrolled patients reaches 262, we will perform statistical analysis on the primary and secondary outcomes. The independent statistical team will be responsible for the interim analysis and report the results to the DSMC. The DSMC will discuss the results and report to the ESEC. If the effectiveness and safety of the experimental group are significantly lower than that of the control group, the study will be suspended.

### Dissemination plans

We plan to publish the results of short-term efficacy and safety studies in 2025, and the results of the long-term follow-up studies in 2030.

### Trial status

The study was registered at the Chinese Clinical Trial Registry (http://www.chictr.org.cn), with number ChiCTR2200057698 on March 15, 2022. Currently, our research team has established the EDC systems to collect clinical data.

## Discussion

LNM is an important factor affecting the 5-year OS rate of gastric cancer patients. Therefore, the prognostic value of D2 lymphadenectomy in gastric cancer needs to be further improved (10). Saito (11) found that in 239 cases of lower-third gastric cancer undergoing D2 lymphadenectomy, the lymph node metastatic rate in the 4sb group was 2.2%, which was related to LNs invasion and advanced gastric cancer. Shu (12) found that the metastasis rate of 12a LNs was 2.67% (11/413), which was related to tumor location, depth of tumor invasion and LNs stage. For patients with advanced gastric cancer (stages III/IV) located in the lower third of the stomach, the metastasis rate of 12a LNs increased to 10.7% (11/103). The recurrence-free survival rate and OS rate of patients with 12a LNM were significantly worse. Other studies have shown that the metastasis rate of 12a LNs is 1.7%–20% and it may be one of the most important factors affecting prognosis (7, 9, 10, 13–15). Therefore, accurate lymphadenectomy plays a positive role in the prognosis. However, the scope of 4sb and 12a LND in D2 lymphadenectomy is not clear. Lin (16) found that the unqualified rate of lymphadenectomy in 948 cases of laparoscopic total gastrectomy was 51.9%, and it gradually decreased with accumulated surgical experience. It is believed that the main reason for the unqualified LNs failure is the failure to dissect LNs at specific locations during the operation. Among them, the failure rate of the 12a LNs was higher (33.44%), and the No.4 LNs were lower (9.39%). This shows that a standardized and clear range of lymphadenectomy is significantly helpful for clinicians treating gastric cancer and undertaking complete D2 lymphadenectomy. However, there are few studies on the cleaning range of 4sb and 12a.

Huang (17) pointed out that the posterior boundary of 12a LND was defined as the anterior edge of the portal vein, so only the LNs in front of the portal vein were cleaned during the operation. Huang (14) published a new 12a LND sequence, suggesting that the portal vein should be exposed first and the LNs before the portal vein should be cleaned. However, we considered that the 12a lymph node metastatic rate is lower for advanced lower third gastric cancer, and LNM around the portal vein is even more rare. Therefore, we suggested that only the LNs area in the front of the PHA should be cleaned, retaining the LNs area around the portal vein. The same is true for the 4sb LNs. We suggested cleaning the LNs around the first branch of the LGA and retaining the LNs around the root of the LGA. Through such a cleaning method, under the premise of ensuring the radical cure of the tumor, the risk of damage to blood vessels and organs, and complications during surgery, are reduced.

Although ESMO, NCCN and JGCA regularly update the guidelines for treating gastric cancer, they are all updated in terms of indications of the extent of LND, and there is no further detailed update of the definition of LND (4–6). In addition, although there have been some studies on 4sb and 12a LNs, the majority are related to LNM and risk factors or survival rates. Therefore, we are currently conducting a clinical trial to establish a safer 4sb and 12a LND range, to reduce the complication rate of D2 lymphadenectomy while obtaining the same radical cure effect.

## Conclusion

The limitations of this study are that the quality of evidence is lower than that of a randomized controlled study and there may be selection bias. However, we will build iterations of future study protocols based on the findings. In addition, we will also recruit more patients to determine more effective 4sb and 12a LND protocols and to provide ideas and evidence for lymphadenectomy in collaboration with other research centers.

## Data Availability

The original contributions presented in the study are included in the article/Suplementary Material, further inquiries can be directed to the corresponding author/s.
